For the past 8 years, our team has provided extensive training and coaching to autism support teachers in the use of several EBPs for children with ASD. The second set of hypotheses relate to teachers’ use of the EBPs in which we have trained them (aim 3). For this aim, we conceptualize TeachTown as a new technology that affects the organizational context and teacher behavior. TeachTown may influence teachers’ attitudes, norms, and self-efficacy about the use of existing EBP (pathway A) and moderate the association between their intentions to use these practices and their behavior (pathway B). Specifically, we hypothesize that introducing TeachTown will negatively affect teachers’ attitudes, norms, and perceptions about using existing EBP, and that teachers will “exnovate” existing practices when they adopt TeachTown. Exnovation refers to the “process whereby an organization decides to divest itself of an innovation that it had previously adopted.” [33–35] Introducing a new technology may result in one of three exnovation outcomes: full exnovation (the new technology completely replaces the previous one so that there is no trace of the previous practice), partial exnovation (the new technology replaces parts or components of the previous practice), or no exnovation (the new technology does not replace the previous practice). We hypothesize that the introduction of TeachTown will result in partial exnovation of EBPs. Teachers may reduce their use of EBP because they think that TeachTown is a reasonable (and easier) substitute for practices like one-to-one instruction or data collection. Our second competing hypothesis is that introducing TeachTown changes the organizational context by giving teachers a tool to provide unsupervised instruction to some students, which would increase the time the teacher has to work with other students. In this case, we would expect use of EBP to increase in classrooms with TeachTown.

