#### Aim 3: exnovation: How does use of existing EBPs change when TeachTown is introduced, and what factors influence this change?

We hypothesize that (1) teachers will decrease the amount of one-to-one teaching incorporated into their daily schedules; (2) teachers will collect less data regarding student performance; and (3) the amount of positive reinforcement, behavior correction, and visual schedules provided by teachers will remain the same. We also will test the hypothesis that TeachTown facilitates EBP use by providing unsupervised instruction for some students, and therefore moderating the association between intentions and use of TeachTown. We will examine whether current EBPs are facilitated or exnovated when TeachTown is introduced and use qualitative methods to understand stakeholder perspectives of exnovation, if relevant. In separate analyses, we will examine whether use of TeachTown affects intentions to use EBP and determinants of those intentions: attitudes, norms and self-efficacy.

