### Overview of current EBPs

As part of our ongoing training and consultation efforts, we train and consult to teachers in five EBPs that are common across most classroom-based autism interventions: discrete trial training, pivotal response training, data collection, positive reinforcement for classroom management, and visual schedules.

*Discrete trial training* is implemented using an intensive one-to-one teaching session in a setting free from distractions. Discrete trial training generally involves the repeated practice of the same response for several successive teaching episodes, breaking down complex skills into component parts, and the use of reinforcers that are functionally unrelated to the response (e.g., providing a token for correctly identifying a car).

*Pivotal response training* uses one-to-one teaching but relies on a less structured teaching environment. It consists of loosely structured sessions that are initiated and paced by the child, take place in a variety of locations, and employ a variety of stimuli. For example, in a situation in which the student wants to play with a toy, he must explicitly request the toy from the teacher.

*Classroom data collection* is a critical component of autism intervention. Each teaching strategy has data sheets to track responses during one-to-one teaching and levels of prompts needed during daily routines.

*Positive behavior support for behavior management* comprises class-wide behavior management techniques. The goal of these strategies is to prevent challenging behavior before it occurs and maximize opportunities for learning. Positive behavior support strategies include the use of visual supports, clear and concrete instructions, timers and cues to signal transitions, and high rates of positive reinforcement for desired behavior paired with low rates of behavior correction for undesired behavior.

*Visual schedules* are used throughout the day. A daily visual schedule for each child is posted in prominent locations and reviewed daily. Visual schedules are used to increase independence and decrease frustration during transitions.

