### Quantitative measures

#### Dependent variables

Accuracy of EBP implementation will be assessed every other month through direct observation in each classroom using fidelity checklists which comprise the most commonly used fidelity measures for these intervention techniques. [52, 62–64] Bachelor’s level research assistants will be trained to 90% reliability on each fidelity measure through didactic instruction and coding of training videos prior to conducting any observations in the field.

*Delivery of one-to-one instruction: discrete trial training and pivotal response training* will be measured through teacher report and direct observation by trained RAs. How much each is used with each student will be measured through teacher report. We will measure accuracy of discrete trial training through monthly direct observations using a fidelity checklist. We will examine quantity and accuracy separately as dependent variables. We also will examine the product of “quantity × accuracy” consistent with our previous evaluations of fidelity for these EBPs [64].

*Data collection* will be measured through observation of completed data sheets. Trained research assistants will record the occurrence of data collection by recording the amount of data collected for each child since the last observation, based on the number of completed data sheets present.

*Positive behavior support strategies* will be measured through direct observation of teacher behavior during regular instructional routines by trained research assistants. RAs will measure teacher’s use of positive reinforcement for desired student behavior using a tool designed to record the amount of praise and behavior correction statements provided by teachers during a 10-min structured observation [65]. Reinforcement will be calculated as a ratio (i.e., the number of praise statements divided by the number of correction statements).

*Visual schedules* will be measured monthly by trained RAs through direct observations based on a fidelity checklist. Use of schedules will be calculated as a ratio of the teacher’s correct use of schedules for each student divided by the total number of students.

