#### *Quantitative data analysis*

The quantitative analysis will take place in three parts, each addressing one of the questions of interest. To address the question of whether TeachTown results in reduced use of EBP, we will compare the intervention and control groups in year 1. We will conduct the analysis at the teacher level. We will create three fidelity variables for each of the five EBPs, as we did in aim 2. The analyses will mirror those described in aim 2. To address the question of whether introducing TeachTown affects intentions to use EBPs, we will conduct similar analyses with intentions to use each of the EBPs at time 2 as the outcomes of interest. If intentions are determined to vary as a function of TeachTown use, we then will explore the effects of TeachTown on each of the determinants of intention.

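### The reinforcement outcome in Aim 3 is a ratio of praise to correction, but the hypothesis is about the amount of each, and the ratio measures neither

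*Protocol article*

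**What the plan says.** The Aim 3 introduction predicts that "the amount of positive reinforcement, behavior correction, and visual schedules provided by teachers will remain the same". This is a statement about amounts, with praise and correction named separately.

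Under Dependent variables, research assistants count "praise and behavior correction statements provided by teachers during a 10-min structured observation". The outcome is then fixed as one figure: "Reinforcement will be calculated as a ratio (i.e., the number of praise statements divided by the number of correction statements". The section does not name either count as an outcome. For one-to-one instruction, by contrast, it says that quantity and accuracy are each examined separately as well as through their product.

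Overview of current EBPs describes the practice being taught as "high rates of positive reinforcement for desired behavior paired with low rates of behavior correction for undesired behavior".

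Under Quantitative data analysis, the year 1 comparison of arms is planned so: "We will conduct the analysis at the teacher level". Three fidelity variables are promised for each of the five practices, but they are not defined as praise and correction counts.

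On timing, the Dependent variables section opens with "Accuracy of EBP implementation will be assessed every other month through direct observation in each classroom". Table 1 gives a monthly schedule for existing EBP fidelity, and the same section later gives monthly observation for discrete trial accuracy and visual schedules. Data collection is measured by "recording the amount of data collected for each child since the last observation".

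**The concern.** Aim 3 asks whether teachers give up existing practices when TeachTown arrives. If children spend part of the day on a computer, teachers may plausibly praise less and correct less together. A quotient of two quantities that move together can stay flat while both shrink. Because the prediction for this practice is no change, an insensitive measure leans towards confirming it.

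The second difficulty is the denominator. Successful behavior support drives corrections down, so the quotient becomes unstable and then undefined as practice improves. At the extreme that the Background defines as "full exnovation (the new technology completely replaces the previous one so that there is no trace of the previous practice", both counts could be zero and the quotient would be 0/0.

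At stake is one of the five practices in Aim 3, not the primary effectiveness result.

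**Working it through.** The article states no figure for this outcome, so there is nothing to reproduce. From the article come the formula (praise divided by correction), the 10-minute window, and 35 and 34 classrooms by arm. Rates of praise and correction are not given; **every rate below is an assumption**.

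**1. What the ratio does when both counts fall.** Start from praise 20 and corrections 5, ratio 20/5 = 4.0, and halve praise to 10:

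| Corrections after | Ratio | Change in ratio |
|---|---|---|
| 2.5 (down 50%) | 10/2.5 = 4.0 | none |
| 2 (down 60%) | 10/2 = 5.0 | up 25% |
| 3 (down 40%) | 10/3 = 3.33 | down 17% |
| 0 | undefined | none can be computed |

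Praise is halved in every row, yet the ratio stays level, rises, falls slightly or ceases to exist. A ratio of 3.33 also arises from 20/6, where praise is unchanged and corrections have risen, so the ratio cannot say which amount moved.

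**2. How often a single window is undefined.** For a Poisson count with mean m, P(0) = exp(−m). For a negative binomial with dispersion k, P(0) = (k/(k+m))^k.

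| Mean corrections per window | Poisson | Negative binomial, k = 2 |
|---|---|---|
| 1 | 37% | 44% |
| 2 | 14% | 25% |
| 3 | 5% | 16% |
| 5 | 0.7% | 8% |
| 10 | about 0% | 3% |

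If counts were summed over, say, five visits before dividing, the Poisson probability would be exp(−5m): 0.7% at m = 1 and 0.005% at m = 2.

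**3. Whether the loss could differ by arm.** Let both counts halve in the TeachTown arm, with k = 4 and one window per teacher. For a control mean of 3 corrections, P(0) is (4/7)^4 = 11% in control and (4/5.5)^4 = 28% with TeachTown. For a control mean of 5 it is (4/9)^4 = 4% and (4/6.5)^4 = 14%.

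**4. What a test would see.** Simulation of 34 control and 35 TeachTown teachers, one window each, k = 4, praise mean 20 in control and 10 with TeachTown, corrections also halved; share of runs with two-sided p < 0.05:

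| Control mean corrections | Praise count | Log ratio, 0.5 added to each count | Raw ratio, undefined values dropped |
|---|---|---|---|
| 5 | over 99% | 5% | 8% |
| 3 | over 99% | 7% | 25% |
| 2 | over 99% | 11% | 42% |

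The ratio of the underlying rates is the same in both arms in every row. The log ratio therefore sits at or near the 5% nominal level while praise has truly halved. The higher figures at low correction rates are artefacts of small denominators and of how zeros are handled; they are not sensitivity to the fall in praise.

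**The case against.** The strongest defence is that the ratio suits the practice: the article describes reinforcement and correction as a pair, and a quotient summarises their balance. Both counts are recorded, so nothing is lost in data collection, and the three fidelity variables promised per practice might include more than the ratio. A rule for zero counts is the sort of detail that a condensed article leaves to an analysis plan.

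Much of this stands. The lack of a zero-count rule is not a fault in itself. The article does not say that ratios are formed window by window and averaged, or that undefined ones are discarded. A reader might infer that the best teachers will be excluded, and differently by arm; the text does not establish that, and pooling over visits would largely remove the problem.

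A reader might also infer that the ratio can never show exnovation when both counts fall. That goes too far: if praise falls proportionally more than correction, the ratio falls, though it understates the loss. It is blind only to roughly proportional falls.

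What the defence does not answer is the mismatch. The balance between two amounts is a different quantity from the amounts, and the hypothesis names the amounts. A zero-count rule or pooling would not change that, and the undefined fidelity variables cannot be credited with separate counts that the article does not mention.

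**Conclusion.** The point holds in a limited form. The reinforcement outcome as defined cannot test the hypothesis as stated, because it measures neither the amount of praise nor the amount of correction. This follows from the definitions and the algebra and needs no assumed rate.

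The frequency of undefined values is uncertain: from about 0% to 37% of single windows for Poisson means of 10 down to 1, higher with overdispersion, and much lower if visits are pooled. The simulation figures likewise depend on assumed rates, one window per teacher and a proportional halving.

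The observation schedule is a separate, minor inconsistency. A two-month interval accrues twice the exposure of a one-month interval, so the data-sheet count has no fixed period. A reader might infer a biased comparison between arms; that would need the arms to be visited at different intervals, and nothing in the article says they are.

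The change is worth making, since it decides what Aim 3 can conclude about this practice, but the primary effectiveness outcome is unaffected.

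**What to change.** - Name the praise count and the correction count as the two outcomes that test the no-change hypothesis. Fit Poisson or negative binomial models with a teacher random effect over repeated visits. While every window is 10 minutes, an offset for observation time adds nothing.
- Keep any praise-to-correction ratio as a secondary descriptive index, formed from counts pooled over a teacher's visits.
- Do not use praise as a share of praise plus correction to test exnovation. It is defined when corrections are zero, but it is just as blind to a proportional fall (20/25 = 10/12.5 = 0.8) and is still undefined at 0/0.
- Separately, reconcile the monthly and every-other-month schedules between Table 1 and the Dependent variables section, and analyse data sheets as a rate per school day since the previous visit.

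The cost is analysis wording. Both counts are already collected; the data-sheet rate needs only the visit dates and the school calendar.

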### Independent variables

*Measures of intentions and determinants of intentions* will be measured as described in aim 2, but asking about the EBPs of interest rather than TeachTown.

#### *Data collection*

Implementation climate and IT infrastructure will be measured at the beginning of each year. Measures of teachers’ intentions, attitudes, perceived norms, and self-efficacy regarding the use of the existing evidence-based practices will be measured in September and April of year 1 for the intervention group and year 2 for the control group. Surveys will be collected directly from the teacher.

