### Participants

#### Teachers

Teachers in the School District of Philadelphia’s K-2 autism support classrooms (*n* = 83) will be recruited. Teachers will participate in TeachTown training as part of their professional development but will not be required to participate in this study. We anticipate recruiting 80% of teachers (69 classrooms). Teachers will be randomly assigned to one of two conditions during year 1 of the study: TeachTown and waitlist. Teachers in the waitlist condition will receive training and support in the use of TeachTown in year 2 of the study.

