### Measures

Our primary outcome of interest, in keeping with recent randomized trials of autism interventions, is cognitive gain. Other selected measures are tied to the domains in which TeachTown purports to affect change (see Table 1).

**Table 1 Tab1:** List of measures, respondents, and time points for data collection

Measure	Respondent	Time point
Aim 1: Effectiveness		
Differential Ability Scales, 2nd Edition (DAS-II)	Direct observation of student functioning completed by graduate student or clinician	Beginning and end of year 1
Bracken Basic Concept Scales, 3rd Edition	Direct observation of student functioning completed by graduate student or clinician	Beginning and end of year 1
Autism Diagnostic Observation Schedule—2nd edition (ADOS-2)	Direct observation of student functioning completed by graduate student or clinician	Throughout year 1
Adaptive Behavior Assessment System, 2nd Edition (ABAS-II)	Teacher rating form of child functioning	Beginning and end of year 1
Pervasive Developmental Disorder Behavior Inventory (PDD-BI)	Teacher rating form of child functioning	Beginning and end of year 1
Social Communication Questionnaire (SCQ)	Parent rating form of child functioning	Beginning of year 1
Family Demographic Questionnaire	Parent	Beginning of year 1
Teacher Demographic Questionnaire	Teacher	Beginning of year 1
Aim 2: Implementation		
TeachTown penetration	Computer software logs	Monthly
TeachTown fidelity	Direct observation of teacher behavior conducted by TeachTown staff	Monthly
Intentions and attitudes scale	Teacher rating scale	Mid-year years 1 and 2
Aim 3: Exnovation		
Existing EBP fidelity	Direct observation of teacher behavior conducted by trained research assistants	Monthly

*Cognitive ability* will be assessed using the Differential Ability Scales, 2nd Edition (DAS-II) [41]. The DAS-II assesses cognitive abilities that are important to learning and may be administered to children ages 2 years 6 months through 17 years 11 months across a broad range of developmental levels. A member of the assessment team will administer the DAS-II to students in the study at the beginning and end of the academic year in year 1.

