#### Quantitative approach

To examine changes in the use of EBP as a result of TeachTown, we will compare the use of EBP in the TeachTown group and control group in year 1. To address the questions of (1) whether increased use of TeachTown results in changes in the use of EBP, (2) TeachTown implementation changes intentions to use other EBP, and (3) whether TeachTown moderates the association between intentions and use of EBPs, we use data from year 1 for the intervention group and year 2 for the waitlist control, so measures will be from the first year that each classroom implements TeachTown.

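### Aim 3's questions on EBP intentions use only each classroom's first TeachTown year, so they lack a concurrent randomized comparator and cannot support the causal wording

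*Protocol article*

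**What the plan says.** The protocol article divides the quantitative part of Aim 3 under *Quantitative approach*. For EBP use the randomized comparison is kept: "we will compare the use of EBP in the TeachTown group and control group in year 1". Three further questions share another data set. Question (1) concerns increased use of TeachTown and change in EBP use. The other two are whether (2) "TeachTown implementation changes intentions to use other EBP, and (3) whether TeachTown moderates the association between intentions and use of EBPs". For all three, "we use data from year 1 for the intervention group and year 2 for the waitlist control", with the stated reason "so measures will be from the first year that each classroom implements TeachTown".

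The *Data collection* section of Aim 3 builds this into the survey schedule. Intentions, attitudes, norms and self-efficacy about the existing EBPs "will be measured in September and April of year 1 for the intervention group and year 2 for the control group". The *Teachers* section fixes the exposure: "Teachers in the waitlist condition will receive training and support in the use of TeachTown in year 2 of the study".

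*Quantitative data analysis* then reads: "To address the question of whether introducing TeachTown affects intentions to use EBPs, we will conduct similar analyses", with intentions at the second time point as outcome. The *Background* states the hypothesis causally: introducing TeachTown is expected to worsen teachers' attitudes, norms and perceptions about existing EBPs.

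**The concern.** The trial randomizes classrooms, and year 1 has an untreated arm. For EBP intentions the plan does not survey that arm in that year. It waits until those teachers have TeachTown too.

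The effect of introducing TeachTown on intentions then has no group showing what intentions would have done without it. The same holds for moderation, because the intention-to-use link is never observed in a classroom-year without TeachTown. This is the proposed mechanism for exnovation, which is one of the three aims and a claimed innovation in the *Discussion*. A fall in intentions over the school year could be reported as caused by TeachTown when it reflects ordinary drift or the EBP training and coaching that the study itself delivers. The missing surveys cannot be recovered once year 1 is over.

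**Working it through.** **Inputs.** 35 TeachTown and 34 control classrooms (*Data analyses*, Aim 1). Teacher-level power of 80% at d = 0.7 with one covariate, r² = 0.15, two-sided alpha 0.05, and d = 0.85 for teacher-level moderators (*Statistical power for quantitative analyses*). Survey timing and exposure as quoted above. Drift and pre-post correlation are not in the document and are assumed over a range.

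**1. The plan's own teacher-level figure.** For a comparison of teacher means, the standard error in SD units is sqrt((1 − r²)(1/35 + 1/34)).
- Without the covariate: sqrt(0.05798) = 0.2408; noncentrality 0.7/0.2408 = 2.91; power 81.7% (noncentral t, 67 df).
- With r² = 0.15: 0.2408 × sqrt(0.85) = 0.2220; noncentrality 3.15; power 87.4%.

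The stated 80% is close to the figure without the covariate, so the statement is conservative. This does not affect the point.

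**2. What is observed, by arm and year.**

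| Arm | Year | TeachTown that year | EBP use observed | EBP intentions surveyed |
|---|---|---|---|---|
| Intervention | 1 | yes | yes | September, April |
| Waitlist | 1 | no | yes | none planned |
| Waitlist | 2 | yes | yes | September, April |

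Only rows 1 and 3 enter questions (2) and (3).

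**3. What those rows can separate.** Let T = 1 if the classroom-year has TeachTown, and let I be intention.
- Effect of having TeachTown, a + bT: T = 1 in all 69 rows, so the design matrix has rank 1 of 2.
- Moderation by having TeachTown, a + bI + cT + d(I × T): rank 2 of 4.
- Intercept, arm and calendar year: the intervention arm is always year 1 and the waitlist arm always year 2, so rank is 2 of 3.
- The same moderation model with both arms surveyed in year 1: rank 4 of 4.

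This concerns having TeachTown against not having it. If T is replaced by amount of use, the models can be fitted, but amount of use was not randomized.

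**4. What September-to-April change is worth on its own.** Assume no TeachTown effect, a drift of δ SD over the school year and pre-post correlation ρ. The paired t-test on 69 teachers has noncentrality δ × sqrt(69)/sqrt(2(1 − ρ)). For δ = 0.2 and ρ = 0.5 this is 0.2 × 8.31/1 = 1.66, and the test is significant 37% of the time. Over the range:

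| Drift (SD) | ρ = 0.3 | ρ = 0.5 | ρ = 0.7 |
|---|---|---|---|
| 0 | 5% | 5% | 5% |
| 0.1 | 11% | 13% | 19% |
| 0.2 | 28% | 37% | 56% |
| 0.3 | 55% | 69% | 89% |

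**5. What a year-1 survey of both arms would give.** For question (2), the effect detectable with 80% power is about (1.996 + 0.847) × 0.2408 = 0.68 without a covariate, and 0.68 × sqrt(0.85) = 0.63 with r² = 0.15. Both lie within the stated d = 0.7. Question (3) is an interaction, for which the plan's own moderator figure of d = 0.85 is the relevant guide.

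**The case against.** The best defence is that pooling first-year classrooms is deliberate and suits a question about dose. TeachTown use is logged and is expected to vary between teachers, and *Quantitative data analysis* speaks of intentions varying with TeachTown use. Association with use, and moderation by use, can be fitted. That stands, so a reader who infers that nothing can be estimated goes too far. But the protocol's own conceptual model has teacher disposition and organizational context driving use, so a dose association does not show what introducing TeachTown does.

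Four other strong readings are tempting and not supported.
- *Every survey comes from an exposed teacher.* Training is at the start of the school year (*Teacher training in TeachTown*), and nothing says whether the September EBP survey comes before or after it. September may be a true baseline. What is missing is a concurrent unexposed group.
- *Table 1 gives a further, conflicting schedule.* The entry "Mid-year years 1 and 2" stands under Aim 2, where the scale concerns intentions to use TeachTown. It is not shown to be the EBP survey.
- *The analysis section promises an arm comparison of intentions.* The text before that sentence refers back to the Aim 2 analyses, which pool both years. An arm comparison is only one reading.
- *Aim 3 discards the randomization.* Its main question, on EBP use, keeps the randomized year-1 comparison.

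It is also fair that effectiveness is the primary outcome and that these mechanism questions are secondary.

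**Conclusion.** The point holds for questions (2) and (3) of Aim 3 and no further. As planned, they have no concurrent randomized comparator, and arm cannot be told apart from calendar year. The uncontrolled change and the observational dose association that remain do not support the causal wording in the *Background* and in *Quantitative data analysis*. The conclusion about the comparator rests only on the stated survey schedule and the waitlist timing. The false-positive rates are illustrations that depend on assumed drift and correlation. The detectable effects treat the 69 teachers as independent, and d = 0.63 to 0.68 applies to question (2) alone.

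This should be fixed, but it does not threaten the trial's main result: neither the primary effectiveness outcome nor the year-1 comparison of EBP use is affected.

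**What to change.** Give the EBP intention and determinant survey to both arms in September of year 1, before TeachTown training, and again in April of year 1.
- Question (2): compare April intentions between arms, adjusted for September.
- Question (3): fit arm, intention and their interaction on year-1 EBP use in all 69 classrooms, and state that power is lower (the plan's d = 0.85 for teacher-level moderators).
- Keep the pooled first-year data, including the year-2 waitlist survey, for the dose question (1) and for description.
- Amend *Quantitative approach*, *Data collection* and *Quantitative data analysis* under Aim 3 to match, and name the comparison group for the intention analysis.

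The cost is two short surveys for about 34 control teachers, whose classrooms are already observed in year 1, plus a wording amendment. If year 1 has passed, label questions (2) and (3) as uncontrolled and exploratory and remove the causal wording.
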